## Abstract

**Background:**

Environmental changes can be positive in mental illness. Systematic, planned and guided environmental change in all its aspects is called nidotherapy. It has shown some benefit but has not been extended to whole communities.

**Aims:**

A cluster-randomised step-wedge trial is planned in six village communities in Nottinghamshire, England, covering an adult population of 400.

**Method:**

Adults in six villages will be offered a full personal environmental assessment followed by agreed change in different 3-month periods over the course of 1 year. All six villages have populations between 51 and 100 residents and are similar demographically. Assessments of mental health, personality status, social function, quality of life and environment satisfaction will be made. After the initial baseline period of 3 months, two villages will be randomised to nidotherapy for 3 months, a further two at 6 months and the last two at 9 months.

**Results:**

The primary outcome will be change in social function; secondary outcomes include health-related quality of life, anxiety and depressive symptoms, personality status, costs of nidotherapy and life satisfaction. Adverse events will also be recorded. The analysis will be carried out using a multimodal statistical approach examining (a) the change in scores of the primary outcome (social function); (b) change in scores of all secondary outcomes, including costs; and (c) changes in environmental satisfaction.

**Conclusions:**

The findings of this study should help to determine whether nidotherapy has a place in the early detection and treatment of mental pathology.

There has been considerable interest in the positive effects of environmental change in the management of mental illness and the promotion of well-being. Many of these have involved exposing people to natural surroundings, particularly the green environment, and there is growing evidence that such interventions improve mental health mainly by reducing depression, anxiety and stress-related symptoms.^
1–5
^ These interventions are not usually introduced for specific health problems in the mentally ill apart from lifestyle elements to improve cardiovascular health.^
2
^ Community studies have also shown that greening unsatisfactory waste environments has a positive impact on the mental functioning of communities.^
6–9
^

However, all of these interventions are decided by external agencies, not by people or patients themselves. Nidotherapy, a planned personal collaborative environmental change, was developed in 2002^
10
^ and has been in use in the National Health Service (NHS) and internationally for 25 years but only in a few limited places. Nidotherapy is an individual therapy but differs from all other psychotherapies in that it focuses entirely on changing the environment, not the person, and has been highly praised for its attention to individual needs.^
11
^ Although it is superficially similar to other environmental interventions such as social prescribing, it differs in that patients themselves choose the environmental interventions they would like to have implemented and the therapist assesses these systematically with good knowledge of an individual’s strengths and weaknesses. The task of the nidotherapist is to evaluate proposed interventions against feasibility, and then help to facilitate their attainment.^
12
^

Nidotherapy has been tested in two small controlled trials, one in people with severe mental illness and the other in people with intellectual disability. The first of these was carried out in patients with severe mental illness and personality disorder in an inner-city service. This showed evidence of cost-effectiveness by reducing hospital in-patient care and promoting better community placement,^
13
^ improving social function in those with comorbid substance use^
14
^ and meriting a Cochrane review.^
15
^ The second trial was carried out in patients with intellectual disability who showed challenging behaviour and, in view of the limited mental capacity of the patients, the training in nidotherapy was carried out with staff. This trial also showed benefit in reducing challenging behaviour compared with the enhanced care programme approach, but the benefits did not appear immediately.^
16
^ There has also been another study showing problems in providing choice in nidotherapy in forensic patients,^
17
^ a series of case studies showing long-term benefit after treatment^
18,19
^ and also the use of nidotherapy in drama.^
20,21
^

The proposed study intends to extend the scope of nidotherapy into a whole population setting where it is recognised that there will be much less serious mental pathology but more opportunity for individual needs to be matched up with those of others in the community. For example, one of the main causes of poor mood in elderly people living alone is loneliness. Interventions to improve this have had limited success^
22
^ but in a community setting environmental interventions to improve social involvement could be made easily if fellow neighbours were able to meet other lonely individuals in common activities. These could be facilitated by nidotherapy.

## Research objectives

The primary objective of the trial is to determine if nidotherapy given in a whole community setting is more effective in improving social function than a mere demonstration of nidotherapy principles in other whole communities. The secondary objectives are to determine if nidotherapy also improves depressive and anxiety symptoms, quality of life, personality functioning and satisfaction with care to a greater extent than just demonstration of principles. We also wish to determine if nidotherapy is cost-effective by recording all the costs associated with its administration.

## Method

The trial design is a cluster-randomised controlled trial using a step-wedge design of nidotherapy to be given to all adult residents (18 or over) in six villages in Nottinghamshire in central England. The plan is to randomise the six villages into three clusters each containing two villages, with active nidotherapy being given to each cluster for a period of 3 months. As the project will explain the principles of nidotherapy from the start of the study, when the people in villages are not receiving active nidotherapy, they will represent an unexposed passive nidotherapy control population.

### Study setting

The six villages are Cotham, Hawton, Kilvington, Alverton, Thorpe and Staunton (total estimated eligible population, 300). Each village has similar population demographic characteristics with most residents over the age of 60, with no economically deprived areas, with most people living in owned properties. Each village has a church but no shops or other amenities.

### Eligibility criteria

The intention is to recruit all who satisfy the eligibility criteria to be involved in the trial in some form.

#### Inclusion criteria

Aged 18 or over living in one of the six identified villages.

#### Exclusion criteria

Impaired mental capacity leading to inability to consent; serious physical illness preventing the possibility of planned environmental change, to be assessed by the clinician and external medical advice; inability to speak English sufficiently well to understand all parts of the trial.

### Recruitment

This will be achieved through village meetings organised by parish groups, leaflets, word-of-mouth snowballing, related events and church communications. Preliminary work has found that general meetings followed by word-of-mouth link-up has been the most productive pathway.

### Statistical design

The trial will use a randomised clustered step-wedge design with two arms. In the first 3-month period, the residents in all villages will be assessed to evaluate their clinical status and their environmental wishes. After 3 months a short check will be made on any material changes since recruitment. Two randomisations will then be carried out in three steps over 1 year. After the first 3 months of baseline assessment, two of the villages will be independently randomised to receive nidotherapy, with the other four acting as unexposed controls. At 6 months, another two villages from the remaining four will be randomised to nidotherapy with the last two unexposed villages as controls; at 9 months these remaining two villages will receive nidotherapy. Thus, the two villages receiving nidotherapy at first randomisation will have three 3-month periods to observe the post-treatment effects, the second two will have two periods to observe the post-treatment effects and the last two villages will have nidotherapy completed 12 months after the trial starts, and a final follow-up will take place for all participants within the following 3 months, and at 6 and 9 months environmental and short clinical assessments will be repeated on all participants.

The analysis will be carried out using intention-to-treat together with imputation of missing data. Analysis will be separated into three components: (a) change in scores of the primary outcome (social function); (b) change in scores of all secondary outcomes, including costs; and (c) changes in environmental satisfaction. Comparison in mean changes of outcomes between the two groups will be conducted using random effects models or multilevel models under a generalised linear modelling framework. Multilevel models^
23
^ will take into account both cluster effects of villages and difference among individuals, while estimating intervention effects over time. Considering that participants are not being randomised into treatment groups, refined models to assess intervention effects could adjust for baseline measures and other possible confounders.

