### Second assessment: three months after nidotherapy input to the first two villages

The SSFQ, PROMIS and ReQoL assessments will be completed for all participants.

*Third assessment: 6 months after completion of baseline assessment and after nidotherapy input to the second two villages*

The SSFQ, PROMIS and ReQoL assessments will be completed for all participants.

*Fourth assessment: 9 months after completion of baseline assessment and after nidotherapy input to the last two villages.*

All the assessments at baseline will be repeated, together with satisfaction scales, including an adverse event scale derived from the work of Klatte et al^
35
^ to determine the nature of adverse events in either arm of the trial. Satisfaction with the village environment will be recorded as a general statement at all assessments and satisfaction with the interventions also assessed using an agreed scale.^
36
^

A record of the most positive and negative environmental events^
37
^ will be made at the termination of the trial and linked to the cost-effectiveness analysis.

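### The stated two-group comparison of mean changes names no calendar-period effect, although exposure in this stepped wedge rises with calendar time

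*Protocol article*

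**What the plan says.** All of this is in the protocol article; no separate analysis plan is at hand.

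- **Design** (Statistical design): "The trial will use a randomised clustered step-wedge design with two arms".
- **Steps** (same section): first "two of the villages will be independently randomised to receive nidotherapy, with the other four acting as unexposed controls"; then "another two villages from the remaining four will be randomised to nidotherapy with the last two unexposed villages as controls"; finally "at 9 months these remaining two villages will receive nidotherapy".
- **Contrast** (same section): "Comparison in mean changes of outcomes between the two groups will be conducted using random effects models or multilevel models".
- **Terms in the model** (same section): the multilevel models "will take into account both cluster effects of villages and difference among individuals, while estimating intervention effects over time".
- **Adjustment** (same section): "refined models to assess intervention effects could adjust for baseline measures and other possible confounders".
- **Timing of measurement**: social function (SSFQ) is measured in all participants at baseline and at three later assessments. The first of these is headed "Second assessment: three months after nidotherapy input to the first two villages". The next two follow the input to the second and the last pair of villages.

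No model equation is given. The words about time qualify the intervention effect; they do not name a term for assessment period.

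**The concern.** A stepped wedge has no two groups that stay apart. Every village starts unexposed and ends exposed, so the exposed state is tied to later calendar time by design. The usual protection is a fixed effect for period. The treatment effect then rests on villages that differ in exposure at the same assessment, together with within-village change corrected for what happened to all villages.

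The article instead describes a two-group comparison of mean change and lists only village and individual effects. Sources of common drift are easy to find in its own text. Assessments are three-monthly, so they fall in different seasons. The same questionnaire is repeated in everyone. Every village receives an explanation of nidotherapy and a mental health assessment from the start. Any of these could move scores in all six villages together. Without a period term, part of that movement would be credited to, or held against, nidotherapy in the primary result.

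**Working it through.** The article gives no model equation, standard deviation, intracluster correlation or sample size calculation, so there is no stated figure to reproduce. The check asks what the treatment coefficient is expected to be when the true effect is zero and all villages share the same time trend.

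**Inputs** (exposure from Statistical design and the assessment headings). Equal 3-month spacing and equal village weights are assumed.

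| Assessment | Periods since baseline, t | Villages exposed | Villages unexposed |
|---|---|---|---|
| 1 | 0 | 0 | 6 |
| 2 | 1 | 2 | 4 |
| 3 | 2 | 4 | 2 |
| 4 | 3 | 6 | 0 |

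The correlation of exposure with assessment number is 0.75.

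**1. Pooled change from baseline, assessments 2 to 4, drift d per period.**
- Mean t, exposed: (2×1 + 4×2 + 6×3)/12 = 28/12 = 2.33
- Mean t, unexposed: (4×1 + 2×2)/6 = 8/6 = 1.33
- Bias: (2.33 − 1.33)d = 1.0d

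**2. Change scores with village fixed effects.** Bias = d × Σ(x − x̄)(t − t̄) / Σ(x − x̄)², summed within villages.
- First pair, exposure 1,1,1: contributes nothing.
- Second pair, 0,1,1: numerator 1, denominator 2/3 per village.
- Third pair, 0,0,1: numerator 1, denominator 2/3 per village.
- Bias: (1 + 1)/(2/3 + 2/3) × d = 1.5d. A village random intercept lies between 1.0d and 1.5d.

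**3. Raw scores at all four assessments.**
- No village correlation: the unexposed mean t is now (6×0 + 4×1 + 2×2)/12 = 0.67, so the bias is (2.33 − 0.67)d = 1.67d.
- Village fixed effects: (1.5 + 2 + 1.5)/(0.75 + 1 + 0.75) × d = 5/2.5 × d = 2.0d.
- Assumed correlations of village means of 0.3, 0.5 and 0.9 give 1.86d, 1.92d and 1.99d.

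**4. Other trend shapes.** In the raw-score model, a one-off shift s after baseline, or at the last assessment only, gives 0.50s (no village correlation) to 0.60s (village fixed effects). A symmetric rise and fall (0,1,1,0) gives 0. That zero belongs to the raw-score model. For pooled change from baseline the same shape gives (2×1 + 4×1 + 6×0)/12 − (4×1 + 2×1)/6 = 0.5 − 1 = −0.5 of its height. A shift straight after baseline gives 1 − 1 = 0, and a shift at the last assessment gives 6/12 − 0 = 0.5.

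**5. With categorical period effects** in the raw-score model, the bias is 0 for every shape tried.

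**6. Precision.** Adding period effects multiplies the standard error by 1.50 (correlation 0) to 1.72 (correlation 0.9), a variance ratio of 2.25 to 2.97.

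**7. Illustration.** A simulation of 1,000 replicates used a raw-score model with person effects. It assumed a within-person correlation of 0.5 and an intracluster correlation of 0.02, with 50 or 67 people per village. These numbers are the article's populations of 300 (Study setting) and 400 (Abstract) divided by six.

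| Drift per period (assumed) | Type I error, no period term | With period terms |
|---|---|---|
| 0 | 4.5% to 5.3% | 3.1% to 4.8% |
| 0.02 SD | 15% to 18% | 5.0% to 5.8% |
| 0.05 SD | 61% to 74% | 4.6% to 5.8% |

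**The case against.** The strongest reply is that silence is being read as exclusion. This is a condensed article, fixed effects are often listed in the analysis plan, and the phrase about estimating effects over time could cover a time term. A reader might infer that the plan omits period and that its primary result will therefore be biased. The article does not support that, since it rules no term out. What remains is that it does state a contrast, between two groups in mean change, and that contrast misdescribes the design whatever a later document adds.

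A second reply is that the two groups may be meant concurrently: two villages against four, then four exposed against two. At assessments 2 and 3 such a comparison has no bias from a common trend. But the article does not restrict the analysis to those assessments, and at the fourth there is nothing to compare with.

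A reader might also infer that every time trend turns into treatment effect, or that the bias has a known direction. Neither holds. The result depends on the shape of the trend and on the model, as step 4 shows. The sign follows a drift that the article does not give, and it describes the population's circumstances as normally stable in the short term. That is some reassurance about secular change, but less about season or repeated questionnaires.

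Finally, the optional wording on baseline adjustment might suggest that the primary result can be chosen after the data are seen. Change scores already use the baseline, and an unseen analysis plan may fix the primary model, so this is not a separate fault.

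**Conclusion.** The concern holds in a limited form. The article states a two-group comparison of mean changes and names village and individual effects but no calendar-period effect, in a design where exposure goes from none to all of the villages over time. If the text were followed without period terms, a sustained common drift of d per period would bias the estimate by 1.0d to 1.5d for the change scores it describes. The larger figures of 1.67d to 2.0d belong to a raw-score model of all four assessments and should not be attached to the change-score wording.

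These multiples follow from the exposure schedule, equal spacing, equal village weights and a trend shared by all villages. The size and sign of any real drift, and the correlations behind the precision and type I error figures, are assumptions. The illustration shows that a small drift could matter; it does not show that one will occur.

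**What to change.** Replace the two-group sentence in Statistical design with a named primary model: SSFQ score at all four assessments, a categorical fixed effect for assessment period, an indicator for the village having crossed over to nidotherapy, and random effects for village and person. Baseline SSFQ enters as the first-period observation, so it needs no separate optional adjustment. Any further covariate models should be labelled supportive.

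The period term is the essential change. Using scores instead of change scores is secondary, because period terms would also remove a common trend from change scores.

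The cost is one paragraph of text, no change in trial conduct, and a standard error about 1.5 to 1.7 times that of the model without period terms under the assumed correlations. That smaller standard error is valid only if there is no time trend. A single crossover indicator also estimates one constant effect. Since the article plans to observe effects over up to three post-treatment periods, it should say whether change with time since crossover will be examined as a secondary analysis.

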#### Nidotherapy villages

The procedure described for all villages will be followed, but in the active nidotherapy villages further assessments before any changes will include an environmental analysis involving social, physical and personal aspects, matching of personality characteristics with the development of an environmental intervention using a formal procedure (or if no intervention is required, a plan for future change) and a timetable (nidopathway) with subsequent monitoring of progress.^
24
^ As the choice of environmental change is made by the patient, the intervention course cannot be predicted in advance; however, in most cases we expect that the main components will be completed within 2 months, and for the purposes of the trial all facilitated interventions will be completed by 3 months.

Nidotherapy will be administered by trained environmental facilitators under the supervision of [name], who has completed training in the subject by a combination of theoretical learning and practice under supervision. This enables a full assessment of personality strengths and motivations and allows the right choice of intervention to follow. Some of the practical aspects of achieving environmental change may also require nidotherapy volunteers who have also been trained in the principles of nidotherapy. Each nidotherapy intervention will be classified by a central team as an individual intervention (one designed for that person or family alone) or a community intervention (defined as one that requires the support and involvement of at least 10 members of the village). In some cases, both individual and community interventions may satisfy these definitions.

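### The multilevel model described has village and person effects but no village-by-period variation; if villages drift differently between quarters, the standard error of the stepped-wedge effect is too small

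*Protocol article*

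**What the plan says.** The Statistical design section of the protocol article plans random effects or multilevel models. It says that these "will take into account both cluster effects of villages and difference among individuals, while estimating intervention effects over time". The only refinement it offers is possible adjustment for baseline measures and other confounders. That changes the mean model, not the correlation structure.

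Villages enter treatment in pairs. First "two of the villages will be independently randomised to receive nidotherapy, with the other four acting as unexposed controls"; then "At 6 months, another two villages from the remaining four will be randomised to nidotherapy with the last two unexposed villages as controls"; the last two follow at 9 months. The Assessments section gives four occasions with the social function score: baseline and three later ones.

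The opening of the Method section uses the word cluster differently: "The plan is to randomise the six villages into three clusters each containing two villages". The Statistical design section speaks instead of cluster effects of villages.

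**The concern.** In a stepped-wedge trial the treatment indicator changes by village and by period. With village and period effects in the model, the nidotherapy effect is estimated from how villages depart from the common time course in particular periods. Chance variation of exactly that kind (village-by-period variation) is therefore the error that matters most.

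A constant village intercept and a constant person intercept cannot absorb it. A model with only these two terms treats every resident's period-to-period deviation as independent of the neighbours' deviations. If something moves a whole village for one quarter, the model counts it as many independent observations. The primary standard error is then too small, and a local event could be declared a nidotherapy effect.

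**Working it through.** The article states no sample size, power, SD, ICC or autocorrelation, so there is no figure of its own to reproduce.

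**Inputs from the article**
- Villages: 6, in three sequences of two. Occasions: 4. Treatment patterns: 0111, 0011, 0001.
- People per village: 300 / 6 = 50 from the Study setting section ("total estimated eligible population, 300"). The abstract's 400 gives 400 / 6 ≈ 67. I also take 25, as if half took part.

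**Assumed inputs** (total variance 1, same people at each occasion, equal village sizes)
- ICC 0.01, 0.05, 0.10.
- Cluster autocorrelation (CAC) 1.0, 0.9, 0.8, 0.5; 1.0 means no drift.
- Correlation of a person's scores over time, given village: 0.6.

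**Closed-form check**

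Let w = ICC × (1 − CAC) be the village-by-period variance, and e = (1 − ICC) × (1 − 0.6) the residual variance. Remove village and period means from the treatment indicator over the 24 cells. Its sum of squares is 2 × (0.3056 + 0.2222 + 0.3056) = 1.667. For the within-village estimator, approximately:
- SE reported by the village-plus-person model = √[(e/n) / 1.667]
- true SE = √[(w + e/n) / 1.667]
- false-positive rate of a z test = 2 × [1 − Φ(1.96 × reported SE / true SE)]

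At n = 50, ICC 0.05, CAC 0.8:
- w = 0.05 × 0.2 = 0.010; e/n = 0.95 × 0.4 / 50 = 0.0076.
- Reported SE = √(0.0076 / 1.667) = 0.0675; true SE = √(0.0176 / 1.667) = 0.1028.
- Ratio 0.657, so the SE is about 34% too small.
- False-positive rate = 2 × [1 − Φ(1.288)] ≈ 0.198.

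**Simulation**

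Null trials (1,500 per setting) were fitted by REML with village and person intercepts, period effects and a two-sided z test at 5%. At the setting above, the mean model SE was 0.067, the actual SD of the estimate was 0.103, and the false-positive rate was 21.0%. This agrees with the formula to within about a point.

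| n per village | ICC | CAC 1.0 | CAC 0.9 | CAC 0.8 | CAC 0.5 |
|---|---|---|---|---|---|
| 25 | 0.01 | 5.8% | 6.5% | 6.5% | 8.3% |
| 25 | 0.05 | 6.1% | 8.8% | 12.8% | 21.3% |
| 25 | 0.10 | 4.6% | 12.9% | 16.8% | 32.1% |
| 50 | 0.01 | 5.5% | 7.3% | 7.3% | 11.9% |
| 50 | 0.05 | 4.9% | 12.8% | 21.0% | 33.3% |
| 50 | 0.10 | 5.3% | 18.7% | 32.3% | 46.7% |

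Sensitivity at ICC 0.05, CAC 0.8: 23.7% with n = 67; with n = 50, 16.2% and 25.9% at person correlations 0.4 and 0.75. Simulation error is about 0.6 points near 5% and 1.3 points near 40%.

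**With the term added**
- Adding a village-by-period random effect and keeping the z test: about 4% to 8% in every setting.
- The same model with t on 4 df: 0.2% to 2.3%, so conservative.
- Regression of the 24 village-period means on village, period and treatment leaves 24 − 6 − 3 − 1 = 14 df. With equal village sizes, normal errors and independent village-period deviations, the t test is exact. Simulation gave about 4% to 6%.
- Allocations for a permutation test: C(6,2) × C(4,2) = 15 × 6 = 90, so the smallest p is about 1/90 = 0.011.

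**The case against.** The strongest reply is that the article excludes nothing. It does not say that village and person are the only random effects, it writes no model equation and it names no test. A journal article condenses a fuller plan, and degrees-of-freedom methods usually belong in the analysis plan. This stands in part. It rules out saying that the trial will use an invalid test, and the absence of a named small-sample method is not in itself a fault. But the article is not silent on correlation: it lists two sources and omits the one on which the design depends, so a model fitted as described would leave it out.

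Second, the documents do not show that drift will be large. The Nidotherapy villages section calls the population relatively stable, with circumstances that normally do not change in the short term. That favours a CAC near 1, where the error rate is about 5%. The point stands as a limit on the size. It is not an argument against allowing for drift.

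Three stronger readings are tempting but unsupported:
- *False positives will be well above 5%.* This needs an ICC and a CAC, and the article gives neither. With ICC 0.01 and CAC 0.8 or higher the rate is only about 6% to 7%.
- *Six villages make the tests invalid.* With six villages and no drift, the z test is close to 5%. With drift modelled, it reaches at most about 8%.
- *The plan's own community interventions prove village-level drift.* Such an intervention is "a community intervention (defined as one that requires the support and involvement of at least 10 members of the village". It is part of nidotherapy, so its impact is a treatment effect, or variation in that effect between villages. It is no evidence of drift when there is no effect, and ten residents are not a whole village.

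On the cluster wording, the three clusters in the Method section can be read as randomisation groups, and the model is already described by village. That makes it a matter of clarity, but one word still carries two meanings.

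**Conclusion.** The concern holds in conditional form. As described, the model leaves out village-by-period variation. If it is fitted that way with a standard z test and villages drift differently between periods, the standard error of the primary effect is too small. Over the assumed range, false positives run from about 5% with no drift to about 47%. At ICC 0.05 and CAC 0.8 they are about 13% (25 per village) to 21% (50 per village).

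These figures rest on assumed ICC, CAC and person correlation, equal village sizes, complete data and four common assessments. Dropout and imputation were not modelled. Severity is moderate: it affects the primary test, but its size depends on drift that the documents do not quantify.

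**What to change.** - In Statistical design, state random effects for village, village-by-period and person, with fixed period effects, and name a small-sample method. One that holds about 5% here is the analysis of village-period means with a t test on 14 df. With unequal village sizes or dropout it is only approximate and should be weighted or checked by simulation. Other degrees-of-freedom corrections, such as Kenward-Roger, were not tested here and should be simulated for this design before one is chosen.
- Add a permutation test over the 90 allocations as support. It is valid if the sequential draw makes all 90 equally likely, which should be stated.
- In Method, call the six villages the clusters and the three pairs the randomisation sequences.

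Only analysis wording changes; trial conduct does not. Intervals become wider. With no drift, moving from 1.96 to the 14 df critical value of 2.145 adds about 9%. At n = 50, ICC 0.05 and CAC 0.8, the interval is about (0.1028 × 2.145) / (0.0675 × 1.96) = 1.67 times as wide, most of which is uncertainty that the narrower interval would hide. The permutation p-value cannot fall below about 0.011. The wording should be settled before outcome data are seen.
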